The FLINT and PIVENS trials provide a good opportunity to investigate this relationship further given their rich dataset and primary analysis that showed no change in HRQoL between active treatment and placebo.^1 2^ These studies provide histological data from liver biopsies before and after the intervention compared with placebo arms, together with data on weight change and quality of life using the SF-36^10^ (a validated quality of life score, covering physical and mental components) at the start and end of the trials. The aim of the study is to investigate the association between disease activity and HRQoL scores in patients with NASH over 1.5 to 2 years. As the SF-36 contains information in different QoL domains, we can investigate specific QoL areas that may be impacted by disease activity.

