# PARTICIPANT IDENTIFICATION

## Study Participants

Adults (18 years and over) with biopsy-proven NASH. This study will include data from all participants in the FLINT and PIVENS trials who have both a baseline and follow-up evaluable biopsy.

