# STATISTICS AND ANALYSIS

## Analysis of Outcome Measures

Data will be presented as mean (SD) or median (IQR) for continuous data and as percentages for categorical variables for the whole sample.

Correlation coefficients (Pearson’s or Spearman’s as appropriate) will be calculated to explore the univariable relationship between change in disease activity (separately for hepatic fibrosis and the NAFLD activity score) and changes in QoL scores (components of SF-36 as per section 4).

In the primary analysis, linear regression models will be used to explore the association between changes in hepatic fibrosis and changes in QoL scores (components of SF-36 as per section 4). Changes in fibrosis stage will be coded as “improved”, “stable”, “worsened”, if there is a change of >=-1, 0, >=+1 in the stage compared with baseline, respectively, as per the cut-offs for clinically meaningful disease changes in NASH clinical trials. Following univariable analysis, all models will be adjusted for sex (binary), age (continuous), baseline BMI (continuous), baseline fibrosis score (continuous), baseline value of the QoL dependent variable in the model (e.g., fatigue), trial (PIVENS or FLINT) and treatment (active vs. placebo), and weight change (continuous). We will also adjust for a dummy variable (able to take integer values 0-5) representing the number of specific co-morbidities (type II diabetes, GI disorder, MSK/ connective tissue disorders, nervous system disorders and psychiatric disorders)

In a secondary analysis, changes in disease activity will be defined as changes in the NAFLD activity score. This change will be coded as “improved”, “stable”, “worsened”, if there is a change of >=-2, -1–1, >=+2 in the stage compared with baseline, respectively, as per the cut-offs for clinically meaningful disease changes in NASH clinical trials. The multivariable models will be adjusted for the same covariates as the primary analysis with the exception of baseline NAFLD activity score instead of baseline fibrosis score. We will also investigate changes in cumulative totals of the physical (physical functioning, physical role, pain and general health) and mental (fatigue, social function, emotional role and emotional well-being) components of SF-36 with disease activity (both change in fibrosis stage and change in NAFLD activity score).

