As SF-36 scores were taken at the same time as the liver biopsy, we anticipate minimal missing SF-36 data. In case of missing HRQoL data at follow-up, we will employ a last observation carried forward approach, since HRQoL was also measured in intermediate time points.

A recent secondary trial analysis (in progress) did not find any evidence of a moderating effect of weight change and change in fibrosis/ NAFLD disease activity score by treatment, trial, or baseline fibrosis score. Therefore, we are not planning to do such moderation analysis. The analysis found evidence of a moderating effect of trial arm (placebo vs. any active treatment) between weight change and NAFLD activity score. We will explore this relationship with the addition of an interaction term; trial arm*weight change.

Sensitivity analysis will be run

1. excluding participants with a diagnosis of no fibrosis at both baseline and end of treatment biopsy
2. complete case analysis (excluding participants with quality-of-life missing data at the biopsy follow up)

There will be no correction for multiple testing and significance will be set at p<0.05.

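### Last observation carried forward is the main-analysis rule for missing follow-up SF-36: it pairs an end-of-treatment biopsy with an earlier quality-of-life score, and multiple imputation would avoid this at little cost

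*Protocol*

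**What the plan says.** Section 7.1 (Analysis of Outcome Measures) states the primary model: "In the primary analysis, linear regression models will be used to explore the association between changes in hepatic fibrosis and changes in QoL scores". Its covariates include weight change and the baseline value of the SF-36 domain being analysed.

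On missing outcomes the same section first says "As SF-36 scores were taken at the same time as the liver biopsy, we anticipate minimal missing SF-36 data", and then that, where follow-up data are missing, "we will employ a last observation carried forward approach, since HRQoL was also measured in intermediate time points". The second of the two listed sensitivity analyses is a "complete case analysis (excluding participants with quality-of-life missing data at the biopsy follow up"). Carrying forward is therefore the main-analysis rule.

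Section 6.1 (Study Participants) takes FLINT and PIVENS participants "who have both a baseline and follow-up evaluable biopsy". Having a follow-up SF-36 is not a condition of entry. The Background describes the biopsy, weight and SF-36 data as available "at the start and end of the trials", and sets the period of interest at 1.5 to 2 years.

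The protocol gives no missing-data rate. It gives no reason to expect stable quality of life after the last observed score, and no rule for a participant whose only SF-36 is the baseline one.

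**The concern.** The quantity of interest is the change in quality of life over the same interval as the change in histology. A participant with a missing follow-up score is in the cohort only because the follow-up biopsy exists. Carrying forward therefore sets an end-of-treatment fibrosis change, and the weight change over the trial, against a quality-of-life change measured over a shorter interval. That breaks the same-time pairing that the protocol itself gives as the reason to expect few missing scores.

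The rule assumes no change in quality of life after the carried visit. The only justification offered is that intermediate scores exist. That makes carrying forward possible, but it does not support the assumption. If no intermediate score exists, a literal reading of the rule records a change of exactly 0, whatever happened to the liver.

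Two things follow for the eight primary domain coefficients, and for the secondary ones. The coefficient is biased if the effect is still developing at the carried visit. And because carried values count as observed follow-up, the standard error does not reflect the missing information.

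**Working it through.** The protocol has no figure to reproduce: it states no missing rate, SD, effect size or standard error. The size has to be worked out under assumptions.

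**From the protocol:** N = 422 (Synopsis); three fibrosis-change categories (improved, stable, worsened); linear regression adjusted for the baseline score; carrying forward as the main rule.

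**Assumed:** improved/stable/worsened 35/40/25%; SD 20 points; correlations 0.7 (baseline–intermediate), 0.7 (intermediate–end) and 0.6 (baseline–end); true improved-versus-stable effect β = 5 points; missing completely at random with fraction q from 2 to 20% (about 8 to 84 of 422 participants).

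**Coefficient.** Let f be the share of the effect already present at the carried visit. In each fibrosis group a fraction 1 − q contributes the full effect and a fraction q contributes f of it, so the expected estimate is

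β × [1 − q(1 − f)].

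A carried baseline score is the case f = 0.

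| q | f = 0.5: formula | f = 0.5: simulated | baseline carried: formula | baseline carried: simulated |
|---|---|---|---|---|
| 2% | 5 × (1 − 0.02 × 0.5) = 4.95 | 4.94 | 5 × 0.98 = 4.90 | 4.85 |
| 5% | 5 × (1 − 0.05 × 0.5) = 4.875 | 4.86 | 5 × 0.95 = 4.75 | 4.76 |
| 10% | 5 × (1 − 0.10 × 0.5) = 4.75 | 4.75 | 5 × 0.90 = 4.50 | 4.51 |
| 20% | 5 × (1 − 0.20 × 0.5) = 4.50 | 4.52 | 5 × 0.80 = 4.00 | 4.03 |

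With an intermediate score carried at f = 0.5, attenuation is 1, 2.5, 5 and 10%. With baseline carried it is 2, 5, 10 and 20%. A separate simulation with other inputs (β = 6, SD 18, 30% exposed) gave 5.64, 5.33 and 4.83 at 5, 10 and 20% missing with baseline carried, that is about 6, 11 and 20%.

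The sign depends on f. At f = 1 the formula returns 5.00 and there is no bias. At f = 1.5 (an effect that peaks early and then wanes) and q = 20% it gives 5 × (1 + 0.20 × 0.5) = 5.50, an overestimate.

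**Standard error of the improved-versus-stable coefficient** (intermediate score carried, f = 0.5). Complete case follows SE(full)/√(1 − q); for example 1.808/√0.80 = 2.02. Multiple imputation used 20 imputations from baseline score, intermediate score and fibrosis change, pooled with Rubin's rules.

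| q | carried forward | multiple imputation | complete case | carried forward vs multiple imputation |
|---|---|---|---|---|
| 2% | 1.80 | 1.82 | 1.82 | about 1% smaller |
| 5% | 1.80 | 1.84 | 1.85 | about 3% smaller |
| 10% | 1.79 | 1.89 | 1.91 | about 5% smaller |
| 20% | 1.78 | 1.99 | 2.02 | about 10% smaller |

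With no data missing the standard error is about 1.81, so at 20% missing the carried-forward analysis reports no loss of precision at all. With baseline carried at 20% it reports 1.66 against 2.02 for complete case, 18% smaller.

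**Coverage of the true 5 points at 20% missing:** 94.5% at f = 0.5; 91.7% if an intermediate score with none of the effect is carried; 90.9% if baseline is carried. Multiple imputation stayed at about 5.0 with coverage of about 94 to 96%.

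**The case against.** The best defence is that the rule will hardly be used. The protocol expects minimal missing SF-36 because the questionnaire was taken with the biopsy, and requiring a follow-up biopsy already removes those who never returned. At 5% missing the bias is 5 − 4.875 = 0.125 points with an intermediate score carried, or 0.25 with baseline carried. Against a standard error of about 1.8 that is 0.07 to 0.14 of a standard error. Complete case is also prespecified, and it is unbiased under the missingness assumed here, so it would show a material discrepancy. These points stand and they limit the severity. They do not remove the point: the expectation has no figure or threshold, the rule applies at any rate, and complete case discards the intermediate scores.

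Three stronger readings are tempting and are not supported.

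- A reader might infer that the Background contradicts section 7.1, since it places SF-36 "at the start and end of the trials". It does not say that SF-36 was measured only then, and section 7.1 says intermediate measurements also exist. The two are compatible.
- A reader might infer that the carried-forward standard error is miscalibrated. For its own estimator it is not: at 20% missing the model value is 1.775 and the sampling SD is 1.774, and coverage is 94.8% when the estimate is unbiased (f = 1). It is too small only relative to a valid analysis of end-of-treatment change. Lost coverage comes mainly from bias.
- A reader might infer that attenuation is certain. It depends on the trajectory of quality of life, which the protocol does not describe.

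**Conclusion.** The point holds, with low to moderate severity. Carrying forward is a weak main-analysis rule here because it breaks the same-time pairing of biopsy and SF-36 and rests on a no-change assumption for which the protocol offers no support. At 2 to 5% missing, which fits the protocol's expectation best, the effect is about 1 to 3% on coefficient and standard error, and about 5 to 6% on the coefficient at the upper end if baseline is carried. At 20% missing it is about 10% on each, or about 20% on the coefficient if baseline is carried.

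These sizes rest on assumed effect, SD, correlations and missing rates, on data missing completely at random, and on half the effect being present at the intermediate visit. The protocol gives none of these. What does not depend on them is the mismatch in timing, and the forced change of 0 if a baseline score is carried.

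**What to change.** In section 7.1, make multiple imputation the main analysis for missing follow-up SF-36. Impute from baseline and intermediate SF-36, change in fibrosis (or in NAFLD activity score, for the secondary models), trial, treatment arm, weight change and the other model covariates, and pool with Rubin's rules. Keep complete case as a sensitivity analysis. Drop carrying forward, or demote it to a second sensitivity analysis, and state that a baseline score is not carried as follow-up. Report, for each domain, how many follow-up scores are missing and how many of those participants have an intermediate score.

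The Background wording on SF-36 timing needs no correction.

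The cost is modest programming with standard routines in R or Stata, which the protocol already plans to use, and slightly wider confidence intervals. No new data are needed. Multiple imputation rests on a missing-at-random assumption, which should be stated.

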# SYNOPSIS

| **Long Study Title** | Association of changes in disease activity and changes in patient-reported quality of life in non-alcoholic steatohepatitis | |
| --- | --- | --- |
| **Short Study Title** | Disease activity and quality of life in non-alcoholic steatohepatitis | |
| **Nature of Study Participants** | Adults diagnosed with non-alcoholic steatohepatitis who participated in previous clinical trials and agreed for data to be shared | |
| **Intended number of participants** | 422 | |
| **Planned Study Period** | February 2021 – May 2021 | |
|  | **Objectives** | **Outcome Measures** |
| **Primary** | **Primary objectives**  To examine the association between changes in disease activity (fibrosis score) and changes in   1. Physical functioning 2. Physical role 3. Pain 4. General health 5. Fatigue 6. Social function 7. Emotional role 8. Emotional well-being | Univariable and multivariable regression coefficients between changes in disease activity (fibrosis score) and changes in   1. Physical functioning 2. Physical role 3. Pain 4. General health 5. Fatigue 6. Social function 7. Emotional role 8. Emotional well-being |
| **Secondary** | **Secondary objectives**   1. Repeat the primary analysis with the NAFLD activity score as a measure of disease activity 2. To examine the association between changes in disease activity (fibrosis and the NAFLD activity score) and changes in 3. SF-36 physical component 4. SF-36 mental component | 1. Univariable and multivariable regression coefficients between changes in disease activity (as NAFLD activity score) and changes in 2. Physical functioning 3. Physical role 4. Pain 5. General health 6. Fatigue 7. Social function 8. Emotional role 9. Emotional well-being 10. Univariable and multivariable regression coefficients between changes in disease activity (fibrosis and the NAFLD activity score) and changes in 11. SF-36 physical component 12. SF-36 mental component |

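### Sensitivity analysis 1 excludes on the follow-up biopsy, so in the fibrosis models the remaining baseline-F0 participants are all worsened and none are stable; a baseline-only exclusion avoids this

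*Protocol*

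**What the plan says.** The protocol's section Study Participants takes everyone in the two source trials "who have both a baseline and follow-up evaluable biopsy". It sets no minimum baseline fibrosis stage.

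The section Analysis of Outcome Measures codes fibrosis change as improved, stable or worsened "if there is a change of >=-1, 0, >=+1 in the stage compared with baseline, respectively". I read the first cut-off as a fall of one stage or more. Univariable models come first. The multivariable models then add covariates that include "baseline BMI (continuous), baseline fibrosis score (continuous), baseline value of the QoL dependent variable in the model", so baseline fibrosis enters as one continuous term.

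The same section lists two sensitivity analyses. The first is run "excluding participants with a diagnosis of no fibrosis at both baseline and end of treatment biopsy". No purpose is stated for it, and it is not limited to the fibrosis models.

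**The concern.** The exclusion uses the end-of-treatment biopsy, which together with the baseline biopsy defines the exposure. Membership of this sensitivity set therefore depends on the exposure category. Among baseline-F0 participants the dependence is complete: stable means out, worsened means in.

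The worsened group then contains baseline-F0 participants and the stable group contains none. A difference between the two groups may reflect worsening fibrosis, or having started without fibrosis. The Background and Rationale names the link between worsening disease and reduced quality of life as an open question, so this contrast matters. A reader who sees the worsened coefficient move in this analysis could not tell whether the primary result is fragile or the exclusion rule caused the move.

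**Working it through.** **Step 1: the cells (no assumed numbers).** The coding and the exclusion give, for baseline F0:

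| Change | Category | Main analysis | Sensitivity analysis 1 |
|---|---|---|---|
| F0 to lower | improved | impossible | impossible |
| F0 to F0 | stable | kept | dropped |
| F0 to F1 or higher | worsened | kept | kept |

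Participants with baseline F1 or higher are untouched. All retained baseline-F0 participants are worsened. Only the stable group changes its membership.

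**Step 2: univariable size.** The protocol gives no stage distribution and no figure to reproduce, so every input here is an assumption: no true association; F0 participants' quality-of-life change differs by *d* points from all others; baseline-F0 share *p*; a proportion *w* of F0 worsen. Stages run 0 to 4. Of those above F0, 40%, 30%, 27.5% and 2.5% are at F1, F2, F3 and F4; 35% improve, and 22% of F1-F3 worsen. The worsening share above F0 is then q = 0.22 × 0.975 = 0.2145.

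F0 share of the worsened group: s = p·w / [p·w + (1 − p)·q]. The stable group has no F0 after the exclusion, so the univariable worsened-versus-stable shift is d × s.

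- p = 5%, w = 40%: s = 0.020 / (0.020 + 0.204) = 0.089. Shift 0.18 (d = 2) or 0.45 (d = 5).
- p = 17%, w = 40%: s = 0.068 / (0.068 + 0.178) = 0.276. Shift 0.55 or 1.38.
- p = 25%, w = 60%: s = 0.150 / (0.150 + 0.161) = 0.483. Shift 0.97 or 2.41.

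**Step 3: adjusted size.** Least squares on the same cells, adding only a linear baseline-stage term, gives these shifts (d = 2 / d = 5):

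| p, w | Worsened vs stable, full sample | Worsened vs stable, planned exclusion | Improved vs stable, full sample | Improved vs stable, planned exclusion |
|---|---|---|---|---|
| 5%, 40% | 0.02 / 0.05 | 0.16 / 0.39 | −0.11 / −0.29 | about 0 |
| 17%, 40% | 0.04 / 0.10 | 0.42 / 1.04 | −0.26 / −0.65 | about 0 |
| 25%, 60% | 0.22 / 0.56 | 0.63 / 1.57 | −0.25 / −0.61 | about 0 |

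Excluding on baseline stage alone gives 0 for both contrasts in every row.

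**Step 4: if the baseline effect is linear.** Take an assumed −1 point per stage, p from 5 to 25% and w from 20 to 60%. Mean baseline stage, worsened minus stable, runs from +0.24 to −0.52 in the full sample and from −0.15 to −0.97 after the planned exclusion. It is about −0.06 after a baseline-only exclusion. Multiplying by −1, the planned exclusion shifts the univariable coefficient by +0.15 to +0.97, against about +0.06 for the baseline-only rule. The adjusted coefficients are unbiased under all three.

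**Step 5: scale.** With an assumed SD of 18 and the intended 422 participants, the adjusted worsened-versus-stable coefficient has a standard error of about 2.3 to 2.4. The largest adjusted shift is 1.57 / 2.4 = 0.65 of a standard error. In the middle row with d = 5 it is 1.04 / 2.4 = 0.43, which puts the false-positive rate near 7% instead of 5%.

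**The case against.** The protocol gives no aim for this check. A reader might infer that it was meant to remove people who cannot improve, and so defeats itself. The text does not say that. Another aim fits at least as well: F0-to-F0 participants never show fibrosis, and calling them stable mixes absent disease with unchanged disease. Dropping that one cell is coherent. This stands, and the point should not be argued from intent.

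Nor does the rule introduce the imbalance. F0 can never be improved, so it is unevenly spread in the main analysis already. The exclusion repairs improved versus stable, as Step 3 shows. This also stands. But the repair costs the worsened-versus-stable contrast, while a baseline-only rule repairs both.

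The selection is on regressors, not on quality-of-life change, so adjusted bias needs a departure from linearity at F0. The planned models also carry baseline quality of life, BMI, weight change, comorbidity count, trial and treatment, which could absorb part of such a departure. Confounding in a deliberately unadjusted model is no surprise. All of this limits the size. It does not restore a stable F0 comparator, and the dropped participants are the ones who would help to check the linear term at F0.

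Finally, in the NAFLD activity score models F0 participants are not worsened by construction. The point is confined to the fibrosis-change models.

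**Conclusion.** The structural point follows from the protocol's wording alone: in the fibrosis-change models, sensitivity analysis 1 leaves baseline F0 only in the worsened category. The rule moves an existing imbalance there.

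The size rests on assumptions, because the F0 share is not given. With 5-25% F0, 40-60% of them worsening and a 2-5 point F0 difference, the spurious worsened-versus-stable shift is about 0.2 to 2.4 points univariable and 0.2 to 1.6 adjusted. With a 5-point difference the low ends are about 0.4 for both. The sign follows the sign of the F0 difference, so the shift can mimic or mask an association. If the baseline effect is linear, the adjusted shift is nil.

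A reader might infer that the adjusted results are biased in any case, or that the primary model is at fault. The documents support neither. This is a low-severity improvement to one supplementary analysis.

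**What to change.** For the fibrosis-change models, define sensitivity analysis 1 on the baseline biopsy only: exclude all participants with baseline fibrosis stage 0. This takes F0 out of all three categories and leaves both contrasts close to balanced on baseline stage.

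The cost is one sentence and a line of code. F0 participants who worsened leave this one analysis but stay in the primary analysis.

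An alternative is to keep the planned exclusion and enter baseline stage as a factor within this sensitivity analysis, at about 3 extra degrees of freedom. The F0 indicator then absorbs the all-worsened F0 group in the adjusted models, but the univariable contrast stays confounded. It is a substitute for the baseline-only rule, not an addition to it, and the primary model needs no change.

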# DATA MANAGEMENT

## Access to Data

Direct access will be granted to authorised representatives from the University of Oxford for monitoring and/or audit of the study to ensure compliance with regulations.

